##### Structural Equation Models

We will use mediation analysis to examine whether depression symptoms mediate ART adherence. We will test for mediation using structural equation models with CIs derived from bootstrapping of indirect and total effects. By applying mediation analyses, we will be simultaneously testing whether the intervention engages the targets and whether intervention-induced changes in targets are associated with clinical benefit. Models will account for baseline scores. For sensitivity analyses, we will use a per-protocol approach to address noncompliance by only including participants who completed the study according to the protocol.

##### App Engagement and Usability

Basic descriptive statistics will be reported for Suubi-Mhealth engagement (session duration and number of modules viewed), as well as app usability scores (USE scores and subscales of efficiency, technical effectiveness, and likability). To determine the relationships between app usability and engagement, we will use linear regression models with an index of engagement (derived from principal components analysis using the above raw metrics of engagement) as the dependent variable and overall usability score as the primary predictor of interest. Demographics associated with both the usability scores and the index of engagement will be included as covariates in the model. In a separate model, we will include each usability subscale (efficiency, technical effectiveness, and satisfaction) rather than the overall usability score in order to explore which subscale might be most predictive of engagement with the mobile app-based tool. In addition, linear mixed models will be used to investigate the association between the intervention engagement index with the primary outcomes over time. Covariance structures for the models will be selected as described above. Effect sizes and 95% CIs will be reported.

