Depression is the most common psychiatric disorder among people living with HIV [6,7]. The prevalence of depression among people living with HIV is estimated to be as high as 63% in SSA [8]. Among young people, the prevalence of major depression is estimated between 16% and 40.8% [9]. Depression is associated with compounding and exacerbating negative HIV outcomes [10,11]. While high levels of ART adherence are necessary for young people to benefit individually from ART, as well as for reducing the risk of HIV transmission, depression has been found to significantly impede ART adherence [10,11]. Previous studies have found that patients with depression are nearly 3 times more likely to be nonadherent to medication regimens than patients without depression [12,13]. Depression can impact ART adherence through isolation from social support, impaired adaptive coping skills, apathy, forgetfulness, and hopelessness [14]. In addition, depression-related fatigue, low energy, inconsistent or lack of sleep, and loss of appetite may make it hard to take ART and attend medical appointments [15]. Indeed, due to limited ART adherence and associated medical complications, patients with depression have a higher risk of increased HIV viral load [16], rapid disease progression, and mortality relative to patients who are not depressed [17,18], making this a crucial population with which to intervene. Thus, failure to address the mental health needs of youths living with HIV, including depression, may lead to costly long-term consequences.

There is growing evidence that depression treatment may improve ART adherence and result in improved HIV outcomes [19,20]. Studies have shown that treating depression was associated with up to 83% higher odds of adhering to HIV treatment [19,21]. Among adults, improvements in cognitive processes have been shown to increase confidence and motivation to engage in HIV management behaviors [22,23]. However, few studies targeting the treatment of depression and evaluating the subsequent improvement in ART adherence have been conducted with adolescents [24], and even fewer studies have been conducted with populations from SSA [25]. Therefore, it is crucial to develop interventions for depression that are tailored to the needs of this specific population, given the prevalence of HIV in the region and the elevated risk factors and myriad barriers to care.

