#### Phase 2, Aim 2: to Examine the Barriers and Facilitators for Integrating Suubi-Mhealth Into Real-World Contexts

##### Overview

Upon completion of the intervention, we will conduct semistructured in-depth interviews with 30 participants upon completion of the intervention to explore their experiences with the intervention as well as barriers and facilitators to implementation and participation. Based on prior research [79], we anticipate that barrier themes may include (1) lack of knowledge and self-efficacy in using mHealth tools; (2) participants’ inability to receive mobile service due to lack of service coverage and connectivity issues; (3) participants’ inability to understand, maintain, or properly use the mHealth tool due to technology literacy issues; and (4) financial sustainability concerns related to the inability to charge a fee for service, bill, or otherwise be reimbursed for services provided via technology. We anticipate that facilitators may include working collaboratively with the app development team to address technical barriers and adapt the app to meet participants’ needs and consistently reviewing app use data to inform progress [80]. The perceived relative advantage of the app over usual care, the ease of use and ability to adapt the app to improve participants’ use, and awareness of participants’ needs and resources will also likely serve as facilitators.

##### Milestone for Phase 2, Aim 2

Completion of an implementation evaluation in which barriers and facilitators are successfully identified as actionable inputs to inform the integration of Suubi-Mhealth into real-world contexts for youths with depression living with HIV. To ensure that this assessment is constructive in facilitating future implementation, we will map each key barrier and facilitator to a relevant implementation strategy identified in the literature to address a similar barrier or leverage a similar facilitator for maximal benefit [96,97]. For example, if the barriers related to service coverage and connectivity issues are mentioned, then the actionable solution will include working with a different service or network provider. This process will yield a concise yet informative implementation toolkit to support future implementation efforts that may face similar patient, provider, and organization-level challenges.

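### The usability-to-engagement regression names only demographics as covariates, leaving out baseline PHQ-9 and clinic, which are already recorded (a minor improvement to a secondary analysis)

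*Protocol article*

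**What the plan says.** The model is set out in the protocol article under App Engagement and Usability (phase 2, aim 1). Its purpose and outcome are given as: "To determine the relationships between app usability and engagement, we will use linear regression models with an index of engagement". The index comes from a principal components analysis of the raw engagement metrics, and the overall usability score is the main predictor. A second model replaces the overall score with the three usability subscales, "in order to explore which subscale might be most predictive of engagement with the mobile app-based tool".

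The covariate rule is one sentence: "Demographics associated with both the usability scores and the index of engagement will be included as covariates in the model". No other covariate is named for this regression. Table 1 lists the sociodemographic questionnaire and the depressive symptom measures (PHQ-9 and BSI) on separate rows, so PHQ-9 is not a demographic in the article's own terms. Clinic is not mentioned in this section. Table 1 has no measure of connectivity.

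Two other places bear on the point:
- The Introduction describes how depression affects treatment-taking: "Depression can impact ART adherence through isolation from social support, impaired adaptive coping skills, apathy, forgetfulness, and hopelessness".
- The phase 2, aim 2 overview expects interview themes to include participants' "inability to receive mobile service due to lack of service coverage and connectivity issues".

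**The concern.** A rule that admits variables associated with both predictor and outcome is a rule for confounders. The difficulty is the pool of candidates. Every enrolled youth has a PHQ-9 score of 10 or more, and severity above that cut will vary. A youth with more severe symptoms may open the app less and also rate it as less easy, useful or satisfying. Youths at one clinic may share network conditions, staff support or phone experience that move both variables together. Followed as written, the rule brings in neither severity nor clinic.

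The entry condition is a second, smaller weakness. If association is judged from the trial data, about 100 youths will often fail to show a modest confounder that is real.

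What is at stake is interpretation. If the coefficient, or the ranking of subscales, is later read as showing which features of the app to improve, part of it may be severity or clinic instead.

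**Working it through.** The article states no figure for this regression, so there is none to reproduce. The question is how large the distortion could be.

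**Inputs from the protocol article**
- 100 youths and 5 clinics per condition (Sample Size and Power), so 100/5 = 20 youths per app-arm clinic on average.
- Intracluster correlation 0.093 (same section). It is given for the depression outcome; using it for usability and engagement is an assumption.
- Entry at PHQ-9 of 10 or more (Inclusion Criteria).

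**Assumptions.** No true link between usability and engagement. Baseline PHQ-9 has correlation −r with each. The article gives no such correlations, so r runs from 0.1 to 0.4.

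**Omitted severity**
- Correlation induced between usability and engagement, which is also the expected standardised slope: (−r)(−r) = r².
- Expected test statistic at n = 100: z = r²√98 / √(1 − r⁴), with √98 = 9.90.
- Approximate rejection rate of a two-sided 5% test: Φ(z − 1.96) + Φ(−z − 1.96).

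| r | slope r² | z | rejection rate |
|---|---|---|---|
| 0.1 | 0.01 | 0.099 | 0.051 |
| 0.2 | 0.04 | 0.396 | 0.068 |
| 0.3 | 0.09 | 0.895 | 0.146 |
| 0.4 | 0.16 | 1.605 | 0.361 |

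Simulation of the same model (20,000 trials per setting) agrees: about 5%, 7%, 14% and 36%. With PHQ-9 in the model the rate is about 5% at every r.

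**Omitted clinic.** Suppose usability and engagement each have intracluster correlation 0.093 across five clinics of 20, with the same clinic effects in both and no link within clinics. In simulation the model without clinic rejects in about 14% of trials; with clinic indicators it rejects in about 5%. Fully shared clinic effects are the extreme case at this intracluster correlation, and partial sharing gives a smaller excess.

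**Screening on association.** Suppose, for illustration, that PHQ-9 were a candidate and had to reach p < 0.05 with both variables; the article states no threshold. In simulation it would enter in 27% of trials at r = 0.2 and 75% at r = 0.3.

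**Cost of adjusting.** One degree of freedom for PHQ-9 and four for five clinics makes five. The unadjusted model has 100 − 2 = 98 residual degrees of freedom. For covariates unrelated to either variable, the standard error grows by √(98/93) = 1.027, or √(98/94) = 1.021 for clinic alone. That is 2–3%.

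**The case against.** A reader might infer that the plan itself names depression and network coverage as shared causes of usability and engagement and then ignores them. The text does not support that. The Introduction ties depression to ART adherence and clinic attendance, and says nothing about app use or app ratings. Coverage appears among expected interview themes about participants' experiences, "as well as barriers and facilitators to implementation and participation", and is not linked to usability scores. Both links to usability ratings, and the link from depression to app use, are inference.

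A reader might also infer that the analysis claims a causal usability effect and would misdirect the app's development. The stated aim is relationships and, for the subscales, exploration of prediction. Read that way, the rejections above are not errors: in those scenarios usability and engagement really are correlated. They mislead only if the coefficient is read as what changing usability would achieve. The article's planned refinement of the app uses phase 1 feedback, before this model is run, and connectivity barriers are handled through the phase 2 interviews.

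Three further objections stand:
- The sentence does not say that only demographics may enter, so it would be too strong to say PHQ-9 can never be included. A fuller analysis plan, not shown, may add covariates.
- The correlations are assumed, and the PHQ-9 entry cut narrows the range of severity, which favours the lower values of r.
- Replacing the rule by a short fixed list would drop other sociodemographic items that it could now admit.

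These objections limit the weight of the point. They do not remove it: the article states a rule for this model, and following it leaves out two recorded variables that are reasonable candidates.

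**Conclusion.** The point holds as a minor improvement to a secondary, associational analysis. The covariate rule covers neither baseline severity nor clinic. If either affects both app use and ratings, the usability coefficient carries part of that effect.

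The size depends on correlations the article does not give. For severity the distortion is negligible at r = 0.1 and small at r = 0.2. It matters from about r = 0.3, where the slope is 0.09 SD per SD and the rejection rate is nearly three times nominal. For clinic, the 14% rests on fully shared effects and on carrying over an intracluster correlation quoted for another outcome. No figure in the article is contradicted, and the primary and secondary outcome comparisons are unaffected.

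**What to change.** Under App Engagement and Usability, change the covariate sentence for both the overall-score model and the subscale model. Prespecify baseline PHQ-9 total and indicators for the five app-arm clinics, in addition to a prespecified list of demographics (at least age and sex). Enter all of them without screening on observed association. State that the usability coefficients are reported as associations.

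This is a wording change and needs no new data. The two additions use about five degrees of freedom and raise the standard error by 2–3%. One limitation should be acknowledged: clinic indicators remove only differences between clinics, so they are a partial proxy for connectivity, which varies between households and is not measured in Table 1. Fuller adjustment for connectivity would need a new questionnaire item.

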##### Sample Size and Power

The primary outcome in aim 1 is whether depression decreases between baseline and postintervention initiation. This is calculated from the depression score change between these 2 time points and categorized as yes versus no. The intracluster correlation for clinics is assumed to be 0.093 and the rate of depression decrease in the control group is 5% [95]. Given our total sample (N=200, 100 youths per condition, 5 clinics per condition), we expect to achieve at least 80% power to detect a rate difference of depression decrease when the rate of depression decrease in the intervention group is 40% and the 2-sided significance level of the test is .05.

##### Milestone for Phase 2, Aim 1

Successful completion of a parallel-group RCT to test the feasibility, acceptability, and preliminary efficacy of Suubi-Mhealth*.* Participants will not experience any adverse events. Participants will have engaged with Suubi-Mhealth daily for 2 months and engaged with at least 75% or more of the modules.

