### Inclusion Criteria

Youths will be eligible to participate if they meet the following criteria: (1) 14-17 years of age with the cognitive ability to understand and comprehend the assenting process; (2) HIV-positive and aware of their status, that is, disclosed to; (3) receiving ART and care from one of the participating clinics; and (4) living within a family, including with extended family members (not in institutions). We will identify youths with depressive symptoms by administering the Patient Health Questionnaire-9 (PHQ-9) [61], which has been validated in rural settings in Uganda [62,63]. Youth scoring ≥10 on the PHQ-9 will be considered for enrollment. Youths will be excluded if they do not meet the inclusion criteria above or are unable to understand the informed consent process, or inability or unwillingness to commit to study completion. Health care providers will be recruited if they are working directly with youths living with HIV at their clinics and agree to participate in the study.

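### The 5% and 40% rates behind the power statement do not fit a primary outcome defined as any fall in depression score in youths enrolled at PHQ-9 of 10 or more

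*Protocol article*

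**What the plan says.** All the power inputs are in the protocol article, Sample Size and Power.

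- **Outcome:** whether depression falls between baseline and a post-intervention point. "This is calculated from the depression score change between these 2 time points and categorized as yes versus no". No size of fall is given. The section does not name the instrument, and Table 1 lists both the PHQ-9 and the BSI for depressive symptoms.
- **Control rate:** "the rate of depression decrease in the control group is 5% [95"], where 95 is a literature citation.
- **App-arm rate:** power is stated for the case where "the rate of depression decrease in the intervention group is 40" per cent.
- **Clustering and size:** "The intracluster correlation for clinics is assumed to be 0.093", with "N=200, 100 youths per condition, 5 clinics per condition".
- **Test:** "the 2-sided significance level of the test is .05". The power claimed is at least 80%.

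Inclusion Criteria sets the entry threshold: "Youth scoring ≥10 on the PHQ-9 will be considered for enrollment". The Mixed-Effect Models section makes linear and generalized linear mixed models, with group, time and their interaction, the principal analysis of primary and secondary outcomes.

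**The concern.** Read as written, a youth who scores one point lower counts as a success. A 5% control rate then requires 95% of untreated youths to score the same or higher at follow-up. A 40% app-arm rate means that 60% of treated youths do not fall by even one point. Neither is credible for a fluctuating symptom score. Ordinary measurement noise moves a large share of people down, and a sample picked for high scores tends to drift down further.

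The power claim depends on the 5%. A rate that low keeps the variance small and leaves room for a 35-point gap that ends at only 40%. If the real control rate is several times higher, the stated power no longer describes the trial's ability to detect a difference in this outcome, and a non-significant result would be read against the wrong benchmark.

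**Working it through.** **Step 1. Reproduce the stated power.** All inputs are from Sample Size and Power.
- Youths per clinic = 100 / 5 = 20.
- Design effect = 1 + (20 − 1) × 0.093 = 2.767.
- Effective n per arm = 100 / 2.767 = 36.14.
- SE = √[(0.05 × 0.95 + 0.40 × 0.60) / 36.14] = √(0.2875 / 36.14) = 0.0892.
- Standardised difference = 0.35 / 0.0892 = 3.92.
- Normal power = Φ(3.92 − 1.96) = 97.5%. A non-central t with 10 − 2 = 8 df (critical value 2.306) gives 92.8%.

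The claim of at least 80% follows from its inputs.

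**Step 2. What control rate fits the outcome as written?** The documents give no PHQ-9 mean, SD or reliability, so these are assumptions: clinic-population mean 6-10, SD 5, retest reliability 0.6-0.9, normal scores rounded and clipped to 0-27, selection at 10 or more, no true change. The documents also do not say whether the screening score serves as baseline, so both cases were simulated.

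| Event in controls, no true change | Screening score is baseline | Baseline re-measured |
|---|---|---|
| Any fall | 48%-69% | 41%-46% |
| Fall of 5 points or more | 3%-32% | 2%-16% |
| Score halved | about 1%-20% | 0.2%-11% |

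A follow-up score below 10, the trial's own entry cut-off, occurs in 13%-47% of those screened in. For comparison, noise with no regression to the mean (assumed standard error of measurement 1-3 points) gives any fall in 36%-45%. No any-fall scenario comes near 5%.

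**Step 3. Dependence on the 5%.** The app arm is held at 40%, with the formulas of step 1.

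| Control rate | Power, normal | Power, 8 df |
|---|---|---|
| 5% | 97.5% | 92.8% |
| 10% | 88% | 79% |
| 15% | 70% | 59% |
| 20% | 48% | 39% |
| 30% | 14% | 12% |

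**Step 4. Power from control rates that fit an any-fall outcome.** Example, 40% v 60%: SE = √[(0.24 + 0.24) / 36.14] = 0.1152; 0.20 / 0.1152 = 1.74; Φ(1.74 − 1.96) = 41%.

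| Control v app | Gap | Power, normal | Power, 8 df |
|---|---|---|---|
| 40% v 60% | 20 points | 41% | 33% |
| 50% v 70% | 20 points | 43% | 35% |
| 60% v 80% | 20 points | 48% | 39% |
| 65% v 85% | 20 points | 52% | 43% |
| 40% v 75% | 35 points | 90% | 80% |
| 50% v 85% | 35 points | 93% | 85% |
| 60% v 95% | 35 points | 97.5% | 92.8% |

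**Step 5. App-arm rate needed for 80% power** (normal, then 8 df): from 20%, 49.8% and 54.0%; from 40%, 71.1% and 74.8%; from 60%, 87.5% and 90.4%.

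**The case against.** The strongest defence is that the text never says that any fall counts. It says the score change is categorised, and a condensed article may leave the cut to the full protocol or analysis plan. The 5% carries a citation that cannot be checked here, and step 2 shows that it is compatible with a responder-type rule such as halving the score. This stands in part. It rules out saying that 5% is wrong under every definition. It does not rescue the paragraph, which states an outcome and a rate that do not match. If the cited source used a stricter rule, its rate has been attached to a different outcome.

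A reader might infer that regression to the mean alone puts controls at 50%-70%. The documents do not support that. The upper part of the range needs the screening score to be the baseline, which is nowhere stated, and noise alone already accounts for 36%-45%.

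Two further points stand as limits. The 20-point gain in step 4 is illustrative; the protocol names no such target. And the trial is a pilot of preliminary impact that will report effect sizes and confidence intervals from mixed models, so interpretation does not rest on the power statement alone. The article nevertheless makes a formal 80% power claim for its primary outcome, and that claim should describe the outcome.

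**Conclusion.** The concern holds as a mismatch between the stated outcome and the rates assumed for it. Under the assumptions in step 2, an any-fall outcome with no true change would occur in roughly 40%-70% of controls, so the planned 40% in the app arm is at or below the untreated rate. The exact range depends on the assumed mean, SD and reliability and on which score is the baseline. That it lies far above 5% does not.

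Two stronger readings are tempting and fail. The first is that the power calculation is miscomputed: it is not, since 5% v 40% gives 97.5% or 92.8%. The second is that the trial is underpowered for any effect: it is not, since a 35-point gap over a 40%-60% base keeps 80% power or more. But that gap requires 75%-95% in the app arm, which is not the planned scenario, and more modest gains such as 20 points have 33%-52% power.

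**What to change.** Base the power statement on the between-arm difference in PHQ-9 score, the kind of contrast the linear mixed model can estimate. State the assumed SD, intracluster correlation and target difference. The article gives no SD or target difference, so the sponsor must supply and justify them.

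If a responder outcome is kept, state its instrument, its time point and the size of fall that counts as yes. One option is a score below the trial's own entry cut-off of 10. Replace the 5%/40% pair with the app-arm rate detectable at 80% power over a credible control range, for example from 20% to about 50%-54% and from 40% to about 71%-75% (normal to 8 df). If the 5% is retained from the cited source, show that the source used the same definition of decrease.

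The cost is a rewritten paragraph and a less favourable stated power. No extra participants are needed.
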